### Statistical analyses

Patients’ socio-demographic and clinical characteristics will be detailed using descriptive statistics. Survival analyses using Cox regression models will be performed to identify potential risk factors for both primary and secondary outcomes. Potential risk factors that will be examined include sex at birth, gender identity, ethnicity, employment and relationship status, criminal history, psychiatric comorbidities (i.e., substance-use disorder, personality disorder), the use of aripiprazole, the use of dopamine partial agonists other than aripiprazole (i.e., brexpiprazole, cariprazine) and the use of any dopamine partial agonists. Cox regression models will be constructed for each of these variables to adjust for potential confounding factors identified using the directed acyclic graph approach. In order to detect a hazard ratio greater than 4 between the use of aripiprazole and the primary outcome with a statistical power of 90% and a bilateral significance level of 5%, 25 events are needed through the follow-up period. The hazard ratio of 4 is considered conservative considering that an odds ratio of 8.6 was observed in our previous nested case-control study [8]. The expected sample size of 800 patients is considered sufficient to observe at least 25 cases of gambling disorder (primary outcome) over the follow-up period given the 3-year prevalence of PBG of 6.4% previously revealed in a similar population [8]. As for the nature and the effectiveness of treatments for PBG and/or gambling disorder, this will be documented for all patients who will have developed either the primary or secondary outcome during the study follow-up period using descriptive statistics.

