The consequences of PBG are manifold and include financial hardship, broken social relationships and isolation, psychological distress and an increased risk of suicide [14, 15]. Although data regarding the consequences of PBG among individuals with a psychotic disorder are scarce, these can certainly be hypothesized as being all the more amplified [16–18]. Indeed, psychotic disorders are associated with several repercussions that can be exacerbated by the concomitant presence of PBG, including an increased rate of suicide and violent acts, stigma, low employment rates, and a 15-to-20-year decrease in life expectancy [19–21]. Not surprisingly, treatment of psychiatric comorbidities, which are common in people with a psychotic disorder, is critical to recovery [22, 23]. Despite this, to our knowledge, there are no tools to screen for PBG specifically tailored to this population, while approaches to treating PBG comorbid to a psychotic disorder are virtually non-existent [24–26]. Findings generated by these unmet needs is a low rate of PBG screening among people with a psychotic disorder by healthcare professionals and suboptimal treatment, hindering their hope for recovery [27–30].

Using an innovative screening and assessment procedure for PBG tailored to young adults with FEP, the main aim of this study is to test the hypothesis that risk factors for PBG in this population include substance use disorders, personality disorders, and the use of aripiprazole or other antipsychotics sharing the same mechanism of action (i.e., partial dopamine agonism). It also aims to demonstrate that current treatments for PBG, which have not been adapted for people with FEP, are currently insufficient to lead to recovery.

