### Independent variables

Variables that will be prospectively extracted from the patients’ medical records include socio-demographic (sex at birth, gender identity, ethnicity, employment status, education level, relationship status, living arrangements, criminal history) and clinical variables (main DSM-5 psychiatric diagnosis, psychotic illness severity as rated by the treating psychiatrist using the Clinical Global Impressions Severity scale, comorbid DSM-5 psychiatric diagnoses, community treatment order, medication treatment, including antipsychotics and all other psychotropic drugs [i.e., antidepressants, benzodiazepines, hypnotics, mood stabilizers, psychostimulants]). Regarding medication, information on both current (i.e., during the follow-up period) and past (i.e., prior to admission in the clinics) drugs will be collected (including dosages, frequency, and route of administration). A patient will be considered exposed to a drug after receiving it for greater than 1 month (or 1 injection in the case of long-acting injectable antipsychotics). Medications administered on an as-needed basis will not be considered. Gambling history (i.e., prior to patients’ admission in the clinics) will be questioned by the case managers as part of the screening procedure for PBG and divided in 3 categories, i.e., none, occasional/recreational, or PBG (i.e., DSM-3 or DSM-4 diagnosis of pathological gambling or DSM-5 diagnosis of gambling disorder). For patients with PBG and/or gambling disorder, the nature of the treatments received for their gambling problematic as well as their effectiveness in resolving it will be documented.

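### The aripiprazole and other-partial-agonist Cox models share no partial-agonist-free reference group, which can hide or reverse the effect of the other agents

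*Protocol article*

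**What the plan says.** The main hypothesis in the Background names as risk factors "the use of aripiprazole or other antipsychotics sharing the same mechanism of action", so aripiprazole, brexpiprazole and cariprazine are all under suspicion.

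The Statistical analyses section then lists as separate potential risk factors "the use of aripiprazole, the use of dopamine partial agonists other than aripiprazole (i.e., brexpiprazole, cariprazine) and the use of any dopamine partial agonists". The third exposure is the union of the first two. On model structure it says: "Cox regression models will be constructed for each of these variables to adjust for potential confounding factors identified using the directed acyclic graph approach". The adjustment sets are not listed.

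Exposure is defined drug by drug under Independent variables: "A patient will be considered exposed to a drug after receiving it for greater than 1 month", or after one injection for long-acting forms. This makes each exposure in effect a yes/no variable. No section says what the unexposed patients are taking, that the categories exclude one another, or that the aripiprazole model adjusts for the other partial agonists or the reverse.

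The event target rests on aripiprazole alone: 25 events to detect a "hazard ratio greater than 4 between the use of aripiprazole and the primary outcome", with 90% power and a two-sided 5% level.

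**The concern.** In a yes/no model for aripiprazole, the patients coded no include users of brexpiprazole and cariprazine. In a yes/no model for those two drugs, the patients coded no include every aripiprazole user, who may account for a large part of the person-time. If the study's own hypothesis is right, both reference groups then contain patients at raised risk, and each hazard ratio is measured against a mixed baseline.

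The two contrasts suffer unequally. Aripiprazole is compared with a group that contains perhaps a few users of the other agents, so its hazard ratio shrinks somewhat. The other agents are compared with a group that may be one third or more aripiprazole users, so a harmful agent can look neutral or protective. That contrast belongs to the main hypothesis. A falsely reassuring result for the other agents could be read as showing that they are safer than they are.

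**Working it through.** **Inputs from the protocol article.** Hazard ratio 4 for aripiprazole, 25 events, 90% power, two-sided 5%, 800 patients and 6.4% over 3 years (all Statistical analyses).

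**Assumptions, not in the document.** Share of person-time on aripiprazole pA = 0.20, 0.33 or 0.50. Share on other partial agonists pB = 0.02 to 0.10. No concurrent use. Hazard relative to no partial agonist: 4 for aripiprazole, and h = 1, 2 or 4 for the others. Neither drug is adjusted for in the other's model.

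**The plan's own figure.** Schoenfeld's formula is D = (1.960 + 1.282)² / [pA(1 − pA)(ln 4)²].
- At pA = 0.50, D = 22.
- At pA = 0.33, D = 10.51 / (0.2211 × 1.922) = 24.7, so 25.
- The share that gives exactly 25 is 0.323 (or its mirror, 0.677).

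The document does not state the share, so 25 cannot be reproduced from its inputs alone. It is consistent with about one third exposed and is not shown to be wrong. This is why 0.33 is used as the middle case.

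**Formulas for the separate models.**
- Aripiprazole: 4 / {[(1 − pA − pB) + pB·h] / (1 − pA)}
- Others: h / {[(1 − pA − pB) + 4pA] / (1 − pB)}
- Any partial agonist: (4pA + h·pB) / (pA + pB)

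**Worked case, pA = 0.33, pB = 0.10, h = 2.**
- Aripiprazole: reference hazard (0.57 + 0.20)/0.67 = 1.149, and 4/1.149 = 3.48.
- Others: reference hazard (0.57 + 1.32)/0.90 = 2.10, and 2/2.10 = 0.95.
- Any: (1.32 + 0.20)/0.43 = 3.53.

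**Full range** (each pair runs from pB = 0.02 to pB = 0.10):

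| pA | True HR, others | Aripiprazole HR seen (true 4) | Others' HR seen | Any HR |
|---|---|---|---|---|
| 0.20 | 1 | 4.00 | 0.62–0.60 | 3.73–3.00 |
| 0.20 | 2 | 3.90–3.56 | 1.24–1.20 | 3.82–3.33 |
| 0.20 | 4 | 3.72–2.91 | 2.48–2.40 | 4.00 |
| 0.33 | 1 | 4.00 | 0.50–0.48 | 3.83–3.30 |
| 0.33 | 2 | 3.88–3.48 | 0.99–0.95 | 3.89–3.53 |
| 0.33 | 4 | 3.67–2.76 | 1.99–1.90 | 4.00 |
| 0.50 | 1 | 4.00 | 0.40–0.38 | 3.88–3.50 |
| 0.50 | 2 | 3.85–3.33 | 0.79–0.75 | 3.92–3.67 |
| 0.50 | 4 | 3.57–2.50 | 1.58–1.50 | 4.00 |

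**Check by simulated Cox fits** (pA = 0.33, pB = 0.10). With h = 2, the separate models gave 3.57 for aripiprazole and 0.96 for the others. One model with both drug terms gave 4.10 and 2.01. With h = 4, the separate models gave 2.87 and 1.87, and the joint model 4.08 and 3.91. The formulas hold, and the joint model recovers the true values.

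**Power for aripiprazole at 25 events, pA = 0.33.** Power = Φ(√(25 × 0.2211) × ln HR − 1.96).
- HR 4: Φ(2.351 × 1.386 − 1.96) = 90.3%.
- pB = 0.02: 89.1% (h = 2) or 86.4% (h = 4).
- pB = 0.10: 83.5% (h = 2) or 66.6% (h = 4).

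**The case against.** The strongest reply is that the flaw is inferred. The article is condensed, lists no adjustment sets, and does not exclude the other drug from them. Taking one partial agonist plausibly changes the chance of taking another and, on the study's own hypothesis, raises the outcome risk, so a directed acyclic graph could well place it in the adjustment set. With both terms in the model, the problem largely goes away. This stands, and it makes the bias conditional. It does not dispose of the point, because the variable list and the one-model-per-variable structure are stated in the article, and nothing there requires the adjustment that would rescue them.

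A reader might infer more than the document supports:
- **That all three hazard ratios are contaminated, or that the class hypothesis cannot be tested.** The unexposed group for any partial agonist contains no user of a suspect drug, so this contrast does address the class hypothesis.
- **That the aripiprazole result could reverse.** Over the ranges tried it is only attenuated, and it is unchanged if the other agents carry no risk. Reversal is confined to the other agents, and occurs only when their true hazard ratio lies below the mean hazard of their mixed reference group. At 20% on aripiprazole, a true 2 stays at 1.20 or above.
- **That adjustment guided by the graph cannot help.** The joint fits show that it can, if it includes the other drug.

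The power figures also take exactly 25 events. The article treats that number as a minimum, and 800 × 0.064 = 51.2 would be expected with full 3-year follow-up, fewer with staggered entry. The power at 25 events is therefore a floor.

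**Conclusion.** The point holds in a limited form and should be fixed. As written, two of the three partial-agonist models lack a clean common reference unless mutual adjustment is added. The serious effect is on the contrast for the other agents. With one third of person-time on aripiprazole, a true doubling of risk all but disappears (0.95–0.99). With one half, it looks protective (0.75–0.79). In the same two settings, agents with no effect appear at 0.38–0.50. This bias depends mainly on aripiprazole's share, so it persists even if few patients take the other drugs.

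The contrast that the study is powered for is affected less. Its hazard ratio falls from 4 to between 2.50 and 3.90 over the whole range tried if the others carry risk. At one third exposed and 2% on other agents, power goes from 90% to 86–89%; at 10% it goes to 67–84%.

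The structure can be read from the text. The sizes cannot: they rest on assumed exposure shares and assumed hazard ratios for the other agents.

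**What to change.** In the Statistical analyses section, replace the two separate yes/no models by one Cox model with a mutually exclusive, time-dependent exposure: no partial agonist (reference), aripiprazole, other partial agonist, both. Report each level against no partial agonist. Entering both drug terms together in one model is equivalent apart from how concurrent use is handled. Keep any versus none as the class contrast.

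The cost is a paragraph of analysis wording. No new data are needed, because all antipsychotics are already being extracted. The reference group for aripiprazole shrinks slightly: at pA = 0.33, from 67% of person-time to 57–65%. For the other agents it shrinks from 90–98% to the same 57–65%, because the aripiprazole users leave it, which is the purpose of the change.

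The estimate for the other agents will be imprecise. At pA = 0.33 and h = 2, the expected number of their events among 25 is 25 × 0.04/2.01 = 0.5 at 2% use and 25 × 0.20/2.09 = 2.4 at 10% use. The change removes the bias, not this imprecision, and the report should say so.

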## Discussion

This prospective multicenter cohort study aims to identify potential risk factors for PBG in young adults with FEP. Among these factors, the causality of the link between the use of aripiprazole, an antipsychotic drug, and PBG, remains to be better documented, to which this prospective study will greatly contribute. Although the comorbidity of PBG and psychotic disorders has been neglected so far, it does nevertheless significantly hinder recovery of the affected individuals. For this reason, results of this study will be crucial to clinicians providing care to people with FEP. The knowledge of potential risk factors will allow them to better prevent and detect the occurrence of PBG. For instance, a better understanding of the possible association between the use of aripiprazole and PBG might ultimately influence the treatment choice through a shared-decision process, even more so in individuals at increased risk for PBG. In addition, to our knowledge, there is no screening instrument for PBG that has been specifically developed for people with FEP, which further contributes to the underestimation of this comorbidity. To this end, the procedure created for this study, which will further be refined following its completion, is expected to be spread out to all FEP programs in the province of Quebec and possibly across Canada. Such a systematic tool, in addition to information provided by the patients’ relatives, is essential for better, and earlier, detection of PBG. Treatment approaches for PBG tailored to people with psychotic disorders are still only at an embryonic phase. Thus, individuals presenting with this comorbidity are usually addressed to standard treatments that have been developed and tested for the general population. While these approaches can be hypothesized as suboptimal for people with FEP, this remains to be documented. Results of this study will hopefully raise the awareness of clinicians and researchers working in this field and serve as the basis to adapted treatments that will better support recovery.

The major strengths of this study include the large sample size and the length of the follow-up period, which should enable us to generate relevant findings. The population study is also representative of the FEP population of the province of Quebec, in part due to the lack of exclusion criteria and necessity to obtain consent as well as the territories served by the 2 study sites, which contain both urban and rural areas. Furthermore, the fact that no informed consent is required prevents a participation bias. Results of this study should thus be readily generalizable. In addition, the exhaustiveness and rigour of the screening and assessment procedure for PBG, as well as collateral information provided by the patients’ relatives, will ensure that the findings are reliable and less prone to detection bias. The prospective design of the study will also allow for a better examination of potential risk factors for PBG in this population and could add evidence to a possible causal link between aripiprazole use and PBG. To this end, the fact that all patients, notwithstanding the antipsychotic drugs received, will benefit from the same screening procedure for PBG will prevent a surveillance bias. The key limitations to this study are (1) previous findings regarding a possible association between PBG and aripiprazole could lead to a decrease in its use, particularly in patients deemed more at risk by clinicians, and thus introduce a prescribing bias, and (2) evaluation of the study outcomes is dependent on the cooperation of clinicians in following the PBG screening procedure. For the first point, while we have no control over the clinical practices and prescribing patterns of psychiatrists, the study will be extended if 25 cases of PBG have not been observed by the end of the recruitment period, i.e., November 1st, 2023. For the second point, a monitoring committee has been set up to closely and regularly follow up with clinicians to ensure that the screening procedure for PBG is being properly followed. Training in the use of this procedure is also provided to all new clinicians arriving during the study. Taken together, these methodological aspects will lead to results that should significantly deepen our understanding of a neglected comorbidity and hopefully positively impact services and care provided to people with FEP.

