### Dependent variables

The primary outcome is the occurrence of a DSM-5 diagnosis of gambling disorder established by the treating psychiatrist. The secondary outcome is the occurrence of PBG, as defined by a score greater than or equal to 8 on the Problem Gambling Severity Index (PGSI) [3], a reliable and validated screening instrument in general population samples which has also been used in previous studies conducted in patients with psychotic disorders [5, 7, 8]. As previously stated, these outcomes are assessed by the case managers and treating psychiatrists using a screening procedure for PBG that has been developed in collaboration with experts on gambling from the *Centre Québécois d’Excellence pour la Prévention et le Traitement du Jeu*. It is a 3-step procedure that includes (1) a screening questionnaire of gambling habits, (2) an evaluation of the severity of the gambling problematic using the PGSI, and (3) a diagnostic interview assessing the DSM-5 gambling disorder diagnosis. The first 2 steps are carried out by the patients’ case managers, while the last step is conducted by the treating psychiatrist on the basis of all available data, i.e., his or her own clinical interview, information obtained during the screening procedure, and collateral information gathered by the case manager from the patients’ relatives. Results of this procedure are recorded in the patients’ medical files and extracted by the research staff.

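### The extension rule counts 25 cases of problem gambling, the secondary outcome, whereas the power calculation needs 25 cases of gambling disorder, the primary outcome

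*Protocol article*

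**What the plan says.** The Dependent variables section defines two separate outcomes. On the first: "The primary outcome is the occurrence of a DSM-5 diagnosis of gambling disorder established by the treating psychiatrist". On the second: "The secondary outcome is the occurrence of PBG, as defined by a score greater than or equal to 8 on the Problem Gambling Severity Index". Case managers score the PGSI. The psychiatrist makes the diagnosis in a later step, drawing on wider information.

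The Statistical analyses section ties the event target to the first of these. It begins "In order to detect a hazard ratio greater than 4 between the use of aripiprazole and the primary outcome" and continues "with a statistical power of 90% and a bilateral significance level of 5%, 25 events are needed through the follow-up period". It then describes 800 patients as "sufficient to observe at least 25 cases of gambling disorder (primary outcome) over the follow-up period", citing a 3-year PBG prevalence of 6.4% from an earlier study.

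The Discussion names possible changes in aripiprazole prescribing as a limitation. Its answer is that "the study will be extended if 25 cases of PBG have not been observed by the end of the recruitment period", with the date given as 1 November 2023. Follow-up ends on 1 May 2024 (Study design).

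**The concern.** The target of 25 is the same in both places, but the outcome counted is not. The power statement needs 25 diagnoses of gambling disorder, while the extension rule asks for 25 cases of PBG. No sentence in the article ties the extension rule to the primary outcome.

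The extension is the article's stated response if events run short. Someone applying it literally would count PGSI scores of 8 or more and could decide against extending while the primary outcome is still below the number on which the 90% power rests.

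**Working it through.** **1. The plan's own figure.** Schoenfeld's formula gives the required events as d = (1.960 + 1.282)² / [(ln 4)² × p(1 − p)] = 5.467 / [p(1 − p)], where p is the share exposed to aripiprazole. The article does not state p.

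- p = 0.50: 5.467 / 0.250 = 21.9, so 22 events
- p = 0.40: 5.467 / 0.240 = 22.8, so 23
- p = 0.323: 5.467 / 0.2187 = 25.0
- p = 0.25: 5.467 / 0.1875 = 29.2, so 30

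The stated 25 therefore fits an exposed share of about one third but cannot be reproduced from the stated inputs alone. The figure is not disputed here. I use p = 0.323 below because it returns the plan's 90% at 25 events; it is an assumption.

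**2. Primary events when the rule is only just met.** Let r be the number of gambling disorder cases divided by the number of PBG cases. The documents give no value. With exactly 25 PBG cases at the check, primary events are d = 25r, and power = Φ(ln 4 × √(d × p(1 − p)) − 1.960).

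| r | Primary events | Power, p = 0.323 | Power, p = 0.50 | Power, p = 0.25 |
|---|---|---|---|---|
| 1.0 | 25 | 90% | 93% | 85% |
| 0.9 | 22.5 | 87% | 91% | 81% |
| 0.8 | 20 | 83% | 87% | 77% |
| 0.7 | 17.5 | 77% | 83% | 71% |
| 0.6 | 15 | 71% | 77% | 64% |

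The first row shows that the exposed share alone moves power between 85% and 93%, even with no mismatch between the outcomes.

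**3. Events added by the end of follow-up.** Assume uniform entry over the four recruitment years, a 3-year cap on follow-up, and a constant hazard giving 6.4% at three years: −ln(1 − 0.064) / 3 = 0.0220 per year.

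- 1 November 2023: mean follow-up 1.875 years, about 32.2 PBG cases expected among 800
- 1 May 2024: mean follow-up 2.219 years, about 38.1 expected

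Events grow by a factor of 38.1 / 32.2 = 1.18. A study that just met the rule would have 25 × 1.18 = 29.5 PBG cases by May 2024. It would reach 25 primary events only if r were at least 25 / 29.5 = 0.85. At r = 0.6 it would have 17.7 primary events (78% power at p = 0.323); at r = 0.8, 23.6 events (88%).

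**4. If PBG occurs at the planned rate.** With 38.1 PBG cases by May 2024, 25 primary events need r of at least 25 / 38.1 = 0.66. At r = 0.6 there would be 0.6 × 38.1 = 22.8 events and about 87% power at p = 0.323.

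**The case against.** The strongest reply is that PBG in the Discussion is an umbrella term and that the authors simply meant the 25 events of the power calculation. The article does use the word loosely. In coding gambling history before admission, it equates PBG with a DSM diagnosis, and the power paragraph supports a gambling disorder count with a PBG prevalence. This may well be what was meant, so a reader should not infer that a trigger on the secondary outcome was deliberately chosen. The wording does not settle it, though: for outcomes during follow-up, the Statistical analyses section itself lists PBG and gambling disorder as alternatives, and Dependent variables gives PBG its own definition.

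A second reply is that the shortfall is hypothetical, and that stands in part. The ratio is unknown. Nothing in the article makes a PGSI score of 8 or more a condition for the diagnosis, so a ratio near or above 1 is not excluded. Just meeting the rule would also mean PBG running below plan, since about 32 cases are expected at the check. Nor is the extension the only protection of power: 800 × 6.4% = 51 cases with full follow-up, or about 38 with staggered entry, already leaves a margin over 25.

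A reader might also infer that checking on 1 November 2023, six months before follow-up ends, weakens the rule. It does not. Events only accumulate, so asking for 25 by November is stricter than asking for 25 by May; at worst the study is extended needlessly.

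**Conclusion.** The mismatch holds on the article's own definitions: as worded, the extension rule can be satisfied with fewer than 25 primary events. The defect is the outcome named in the rule, not its date.

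The size cannot be fixed from the documents. The 71% to 90% range is an illustration for the boundary case of exactly 25 PBG cases, an assumed ratio of 60% to 100% and an assumed exposed share of about one third, all at the November 2023 check. It is not a forecast of the study's power. Later events would raise it, and at the planned PBG rate the loss is small or absent unless the ratio falls below about 66%. A reader might conclude that the study will be underpowered; the documents do not support that. What they support is that the rule, when event rates run low, does not protect the analysis for which the 25 events were calculated. Severity: should fix.

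**What to change.** In the Discussion sentence, replace the 25 cases of PBG with 25 incident cases of DSM-5 gambling disorder (primary outcome), matching the Statistical analyses section. Keep the check at 1 November 2023. Moving it to May 2024, or allowing projected cases to count, would loosen the rule.

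The edit is one phrase. The cost is that an extension becomes somewhat more likely. At the planned PBG rate, the rule as worded would expect about 32 cases and no extension; the corrected rule would extend if the ratio were below about 25 / 32.2 = 0.78. For ratios between about 0.66 and 0.78 that extension would prove unnecessary on expected counts, because 25 primary events would be reached by May 2024 anyway.
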